#### Length of stay and total hospitalization costs

The LOS will be recorded from the day of admission to discharge. Total hospitalization cost will be defined as the total payment that the patients’ primary insurance carrier provides to the hospital.

#### Adverse events

Each patient will be screened with clinical symptoms (acute onset, swelling, sever pain) and physical examination (significant tenderness at the femoral triangle or/and leg) to ensure no deep vein thrombosis (DVT) is present. Doppler ultrasound in diagnosis of venous thrombosis of lower extremities will be performed at the time of hospital discharge, and repeated at 2 weeks and 3 months after TKA.

Pulmonary embolism (PE) will be investigated by clinical signs and symptoms (cough, hemoptysis, chest tightness, tachypnea, shock, dizziness, cyanosis, etc.). Patient with clinically suspected PE will undergo a contrast-enhanced chest CT scan immediately.

The wound complications (ecchymosis, bleeding, local hematoma, superficial and deep infection) will be carefully recorded during hospitalization and follow-up period.

### Data management

Each participant’s identification number and baseline data will be electronically contained in CRFs. Outcome data will be put in the CRF by two independent trained research assistants with a double-entry method. No personal data will be shared with any other outside party.

### Sample size calculation

Sample size was estimated based on a large database generated from a prospective multicenter study sponsored by the Chinese Health Ministry (project number 201302007) using PASS 2011 (NCSS, LLC. Kaysville, Utah, USA) software. According to the database, the TBL was 730.96 ± 262.85 mL, with a single dose of TXA before TKA in RA patients. To detect a difference of 200 mL of primary end point, with a power of 0.90 and the significance level of 0.05, 31 patients per arm will be needed. Considering a dropout rate of 20%, we decided to involve 39 patients in each arm.

### Statistical analysis

Statistical analyses will be performed using SPSS version 24 (SPSS Inc. USA) software. We will use the independent samples t-test (Student’s t-test) to evaluate quantitative data with normal distribution, and use Mann–Whitney U-test for data not having normal distribution. Pearson Chi-square test or Fisher exact test will be used to analyze qualitative comparative data. *P* values will be judged significant if they are less than 0.05.

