### Study interventions

Group A: 100 mL normal saline (NS) will be administrated intravenously twice daily starting from 3 days before the operation (performed by a nurse). 1.5 g of TXA will be given 30 min before the operation (performed by an anesthetist).Group B: 1.5 g of TXA will be given twice daily starting from 3 days before the operation (performed by a nurse). 1.5 g of TXA will be given 30 min before the operation (performed by an anesthetist).

TXA is produced by Chongqing Lummy Pharmaceutical Co., Ltd., and used according to the second edition of 2015 Chinese Pharmacopoeia and Drug Supplement Application Approval YBH19712005; the approval number is National Drug Standard H20056600.

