### Secondary outcomes

#### Fibrinolysis parameters, inflammatory markers and coagulation parameters

Fibrinolysis parameters [fibrin(−ogen) degradation products (FDP), D-dimer], inflammatory markers [erythrocyte sedimentation rate (ESR), C-reactive protein (CRP), interleukin-6 (IL-6)] and coagulation parameters [activated partial thromboplastin time (APTT), prothrombin time (PT) and thrombelastography (TEG)] will be tested 1 and 3 days before surgery and 1, 2, 3 and 14 days after surgery. All measurements will be performed by the Department of Clinical Laboratory of The First Affiliated Hospital of Chongqing Medical University.

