#### Post-operative pain score and analgesia usage

Pain level at rest (rest in bed at least for 30 min before test) and during activity (from sitting to standing position) will be assessed using a visual analogue scale (0 means no pain, 10 means severe pain imaginable) and will be conducted 1 and 3 days before surgery and 1, 2, 3 and 14 days after surgery, and the analgesia usage will be carefully recorded.

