## Discussion

To our best knowledge, this will be one of the first attempt to compare the effects of preemptive antifibrinolysis of single-dose and repeat-dose TXA in RA patients undergoing TKA. The hemostatic effect of TXA has been well-established in OA patients undergoing TKA [9, 10, 32]. However, the efficacy and safety of TXA in RA patients is still undetermined. Compared with OA patients, RA patients are at a higher risk of requiring blood transfusion [11, 12]. Mukubo et al. found that D-dimer in RA patients was ten times normal, indicating a hyperfibrinolytic state in RA patients prior to surgery [21]. In addition, fibrinolysis can also be caused by surgical trauma and enhanced by tourniquet [9]. Since fibrinolytic activation is a cascade process and is most easily inhibited at its early stage [33], the preoperative dose has been deemed as the most significant dose [23, 34]. Hourlier et al. indicated that the reason why the previous studies failed to show the efficacy of single-dose treatment may owe to the lack of dosage [35]. Therefore, we assume that repeat-dose preoperative TXA may exert an auxiliary antifibrinolytic effect. In this trial, different preoperative dosing regimen will be compared, which will contribute to the formulation of further recommendations on the use of TXA for reducing blood loss in RA patients undergoing TKA.

RA is characterized by persistent synovitis and systemic inflammation, which may lead to joint deformity and disability [36, 37]. In addition, since inflammation and atherosclerosis are closely linked, it is reported that satisfactory inflammation control is likely to decrease the cardiovascular risk in patients with RA [38]. Despite numerous studies proving the effect of TXA on fibrinolysis, it still remains unclear in terms of its anti-inflammatory properties [9, 17, 39]. Data from previous studies showed that D-dimer could stimulate monocytes to synthesize and release IL-6, indicating that there is a close connection between fibrinolysis and inflammation [40, 41]. Jimenez et al. found that double-dose TXA could prolong the inhibition of fibrinolysis and alleviate postoperative inflammation in cardiopulmonary bypass (CPB) patients [42]. However, evidence is scarce in RA patients with regard to the anti-inflammatory effect of TXA. In this trial, we will compare different preoperative TXA regimens, suspecting that repeat-dose preoperative TXA could provide additional inflammation control.

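### Repeatedly measured secondary outcomes are left to unadjusted two-group tests, each judged at 0.05; if each visit is tested, the 12 inflammation comparisons have about a 19–46% chance of at least one false positive

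*Protocol article*

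**What the plan says.** For quantitative outcomes, the Statistical analysis section of the protocol article offers two methods. The first reads "We will use the independent samples t-test (Student’s t-test) to evaluate quantitative data with normal distribution". Where normality fails, the stated alternative is to "use Mann–Whitney U-test for data not having normal distribution". One threshold then covers every outcome, primary or secondary: P "values will be judged significant if they are less than 0.05". Neither test uses a baseline value.

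Under Secondary outcomes, the laboratory measures, among them "inflammatory markers [erythrocyte sedimentation rate (ESR), C-reactive protein (CRP), interleukin-6 (IL-6", "will be tested 1 and 3 days before surgery and 1, 2, 3 and 14 days after surgery". The two pain scores follow the same timetable ("will be conducted 1 and 3 days before surgery and 1, 2, 3 and 14 days after surgery"), and Table 1 agrees. Under Study interventions, Group B's repeat dosing has begun by the second preoperative sample: "1.5 g of TXA will be given twice daily starting from 3 days before the operation". Only the sample three days before surgery (Pre-D3) can therefore serve as a baseline; the one on the day before surgery (Pre-D1) falls on treatment.

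The Discussion attaches a directional expectation to the inflammatory markers: "suspecting that repeat-dose preoperative TXA could provide additional inflammation control". No outcome is described as exploratory.

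**The concern.** A two-sample test takes one value per patient. The article has six values per patient for each of these measures and does not say how they become one. The simplest way to apply the stated tests to the stated schedule is one test per measure per visit, each at the full 0.05.

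Two things follow.

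- **Interpretation.** If the regimens do not differ in their effect on inflammation, one marker on one day may still fall below 0.05, and the stated rule allows it to be called significant. Markers and days may also disagree, and the article does not say which of them answers the question.
- **Efficiency.** Daily unadjusted tests ignore a baseline that is already being collected and do not pool neighbouring days. In a trial of 39 per arm this costs precision and leaves chance baseline differences uncorrected.

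The point concerns the secondary outcomes only. The blood-loss outcomes and the sample size are not affected.

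**Working it through.** The article states no error rate for these outcomes, so there is no figure of its own to reproduce.

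**Inputs from the article**
- Threshold 0.05. Sidedness is not stated; two-sided is assumed.
- Laboratory measures: FDP, D-dimer; ESR, CRP, IL-6; APTT, PT, TEG (counted as one) = 8. Pain scores: rest, activity = 2. Total 10.
- Times: Pre-D3 (baseline), Pre-D1 (on treatment), and days 1, 2, 3 and 14 after surgery.

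**Input assumed.** Correlations between test statistics are not given, so a range is shown.

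**Number of tests, if each visit is tested**
- Inflammation, postoperative: 3 × 4 = 12. With Pre-D1: 3 × 5 = 15.
- All ten measures, postoperative: 10 × 4 = 40.

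**Expected false positives** (no correlation assumption needed): 12 × 0.05 = 0.6.

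**Chance of at least one P<0.05 under no effect, 12 tests**
- Independent: 1 − 0.95^12 = 0.460.
- Correlated: simulated standard normal statistics, counting sets with any |z| > 1.96.

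| Assumed correlation | At least one P<0.05 |
|---|---|
| 0 | 46% |
| 0.5 common | 32% |
| 0.8 common | 19% |
| 0.5 between markers, 0.7 between visits | 30% |

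**Only results favouring repeat dosing** (one tail, 0.025 each)
- At 0.5 between markers and 0.7 between visits: about 15%.
- Independent: 1 − 0.975^12 = 0.262.

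**Adding Pre-D1 (15 tests)**
- Independent: 1 − 0.95^15 = 0.537.
- At 0.5 and 0.7: 34% in either direction, 17% favouring repeat dosing.

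**All ten measures, 40 postoperative tests:** 1 − 0.95^40 = 87% if independent, 59% at 0.5 and 0.7. These are for context; no single claim rests on all 40.

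**What one adjusted comparison gains**
- The standard error of a chance baseline difference, in standard deviation units, is √(2/39) = 0.23 with 39 per arm and √(2/31) = 0.25 with 31. A baseline gap of a quarter of a standard deviation is therefore ordinary at this size, and the stated tests do not correct for it.
- Let c be the correlation among days 1–3 and b the correlation of each day with baseline. Relative to a single unadjusted day, and with equal variances, the baseline-adjusted three-day mean has variance (1 + 2c)/3 − b². With c = 0.7 this is 2.4/3 = 0.80 if b = 0, and 0.80 − 0.25 = 0.55 if b = 0.5. Both b values are assumed for illustration.
- A single named comparison has an error rate of 5%. Bonferroni over the 12 tests would also hold the error, at 1 − (1 − 0.05/12)^12 = 4.9% if independent, but would still use neither the baseline nor the pooling.

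**The case against.** The strongest reply is that this is a condensed protocol article. Lead visits, repeated-measures models and multiplicity for secondary outcomes are commonly left to a statistical analysis plan, which is not shown. The outcomes are plainly labelled secondary, blood loss is the primary, and family-wise control across secondaries is not normally required. A t-test could also be applied to a change score or an average.

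Much of this stands, and it rules out several stronger readings that a reader might infer.

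- **That the plan commits to testing every visit.** It does not say so; this is an inference from the named tests and the schedule.
- **That an anti-inflammatory conclusion is planned.** The Discussion voices a suspicion. It sets no success rule, and nothing says that one significant marker on one day would prove the effect.
- **That the absence of a multiplicity correction is itself an error.** For labelled secondary outcomes it is a matter of choice, as is testing them only after a positive primary result.
- **That 46% is the realistic risk.** It assumes independence between markers and days in the same patients, which is implausible. It is the top of the range for the 12 tests.

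What the reply does not remove is that the article has already stated a method and a threshold that reach every secondary outcome. An analysis plan that used the baseline, or confined significance to chosen comparisons, would have to depart from or narrow that statement.

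**Conclusion.** The point holds as a recommended improvement to a stated method. The article applies unadjusted two-group tests and a blanket 0.05 to outcomes that have a baseline and several later measurements.

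If visits are tested separately, the 12 postoperative inflammation comparisons carry about a 19–46% chance of at least one nominal P<0.05 under no effect, over assumed correlations of 0.8 to 0. The chance of one favouring repeat dosing is about 15% at 0.5 between markers and 0.7 between visits. The figures rest on two-sided tests, no true effect on any of the three markers, and correlations that the article does not give. They are chances of a nominal result, and become a false conclusion only if such a result is read as proof.

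Even at the lowest figure, the chance is nearly four times 5%. The case for a baseline-adjusted comparison also does not depend on the multiplicity argument.

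**What to change.** In the Statistical analysis section:

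1. For each repeatedly measured secondary, specify one between-group comparison adjusted for the Pre-D3 value: ANCOVA on the mean of days 1–3, or a repeated-measures model, on the log scale where the measure is skewed. Pre-D1 should not be the baseline, because repeat dosing has already begun; the adjustment presumes that the Pre-D3 sample precedes the first infusion.
2. If an inflammation claim is intended, name one marker as the lead (CRP, for example) and confine the significance statement for inflammation to it.
3. Report individual-visit comparisons, including Pre-D1 and day 14, as exploratory differences with 95% confidence intervals and no significance claim.

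Testing the lead marker only after a positive primary result is optional.

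The cost is a few sentences and a little model code, with no extra patients, visits or samples. The small downside is that an isolated single-day difference can no longer be claimed as significant.

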### Ethics and dissemination

This clinical trial has been approved by the ethics committee of the First Affiliated Hospital of Chongqing Medical University (2019–015). The data will be published on the website of the China Clinical Trials Registry and the results of this study will be published in a peer-reviewed journal in accordance with CONSORT, and disseminated at relevant national and international conferences.

## Discussion

To our best knowledge, this will be one of the first attempt to compare the effects of preemptive antifibrinolysis of single-dose and repeat-dose TXA in RA patients undergoing TKA. The hemostatic effect of TXA has been well-established in OA patients undergoing TKA [9, 10, 32]. However, the efficacy and safety of TXA in RA patients is still undetermined. Compared with OA patients, RA patients are at a higher risk of requiring blood transfusion [11, 12]. Mukubo et al. found that D-dimer in RA patients was ten times normal, indicating a hyperfibrinolytic state in RA patients prior to surgery [21]. In addition, fibrinolysis can also be caused by surgical trauma and enhanced by tourniquet [9]. Since fibrinolytic activation is a cascade process and is most easily inhibited at its early stage [33], the preoperative dose has been deemed as the most significant dose [23, 34]. Hourlier et al. indicated that the reason why the previous studies failed to show the efficacy of single-dose treatment may owe to the lack of dosage [35]. Therefore, we assume that repeat-dose preoperative TXA may exert an auxiliary antifibrinolytic effect. In this trial, different preoperative dosing regimen will be compared, which will contribute to the formulation of further recommendations on the use of TXA for reducing blood loss in RA patients undergoing TKA.

RA is characterized by persistent synovitis and systemic inflammation, which may lead to joint deformity and disability [36, 37]. In addition, since inflammation and atherosclerosis are closely linked, it is reported that satisfactory inflammation control is likely to decrease the cardiovascular risk in patients with RA [38]. Despite numerous studies proving the effect of TXA on fibrinolysis, it still remains unclear in terms of its anti-inflammatory properties [9, 17, 39]. Data from previous studies showed that D-dimer could stimulate monocytes to synthesize and release IL-6, indicating that there is a close connection between fibrinolysis and inflammation [40, 41]. Jimenez et al. found that double-dose TXA could prolong the inhibition of fibrinolysis and alleviate postoperative inflammation in cardiopulmonary bypass (CPB) patients [42]. However, evidence is scarce in RA patients with regard to the anti-inflammatory effect of TXA. In this trial, we will compare different preoperative TXA regimens, suspecting that repeat-dose preoperative TXA could provide additional inflammation control.

A number of previous studies have demonstrated the presence of preoperative blood hypercoagulability in RA patients, which is a risk factor of postoperative venous thromboembolism (VTE) [43]. In addition, concerns about the potential pro-coagulation effect of TXA in this high-risk patient population still hinder the wide application of this medication in TKA [44]. Therefore, we plan a prospective randomized controlled study to evaluate the safety of different TXA regimens in RA patients undergoing TKA. In this study, we will use APTT, PT and TEG to detect perioperative blood hypercoagulability in patients with RA, which may provide some insights to assess the safety of TXA in RA patients.

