**Methods/design:**

The study will be a double-blind randomized controlled trial with two parallel groups of RA patients. Group A will be given 100 ml normal saline twice daily starting from 3 days before the operation, Group B will be given TXA 1.5 g twice daily starting from 3 days before the operation. All patients will be given TXA 1.5 g 30 min before the operation. The primary outcomes will be evaluated with total blood loss and hidden blood loss. Other outcome measurements such as, fibrinolysis parameters, inflammatory factors, visual analogue scale for post-operative pain, analgesia usage, coagulation parameters, transfusion, the length of stay (LOS), total hospitalization costs, the incidence of thromboembolic events and other complications will be recorded and compared. Recruitment is scheduled to begin on 1 August 2020, and the study will continue until 31 May 2021.

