**Discussion:**

In current literature there is a lack of evidence with regard to the efficacy of TXA in RA patients. The findings of this study, whether positive or negative, will contribute to the formulation of further recommendations on the use of TXA in RA patients undergoing TKA.

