## Background

As the one of the most common inflammatory arthritis affecting about 1% of world population [1, 2], rheumatoid arthritis (RA) is associated with an increasing socioeconomic impact and often affects the diarthrodial joints, including knee joint [3, 4]. Total knee arthroplasty (TKA) is considered one of the most effective orthopedic health care interventions for patients with rheumatoid arthritis (RA) [5–8], and RA patients achieve better satisfaction after TKA compared to patients with osteoarthritis (OA) [8]. However, fibrinolysis stimulated by surgical trauma could lead to significant blood loss [9, 10], and RA patients undergoing this procedure tend to have a higher risk of requiring transfusion than OA patients, owing to preoperative anemia, lower average weight, great bone mass loss, complete synovectomy and extensive soft tissue separation [11, 12]. Blood transfusion is often associated with infectious or noninfectious complications [13], and can prolonged hospital stays, delay recovery and increase medical expenses [14]. Therefore, decreasing blood loss, which can subsequently reduce the requirement for transfusion, is extremely important for patient to improve the quality of life.

As an antifibrinolytic agent, the hemostatic effect of tranexamic acid (TXA) has been proven in TKA [9, 10, 15]. However, in view of the fact that almost 97% of TKAs are performed for OA [16], current published studies in terms of the efficacy of TXA were mainly based on the experience in OA patients [9, 17–20], and there still exists a paucity of evidence with regard to the efficacy of TXA in RA patients. Unlike OA, RA has its own features in the aspects of pathogenesis, prognosis, and medical management [5]. It has been reported that RA patients had higher preoperative D-dimer value than OA patients [21]. Therefore, TXA is theoretically more suitable for RA patients compared to OA patients, and a specially designed TXA scheme for RA patients with TKA is urgently needed.

The most common preoperative protocol of TXA in TKA is to administer one single dose prior to skin incision [9, 22–24], which might seem to be insufficient to inhibit fibrinolysis in RA patients. Therefore, we plan to conduct a randomized clinical trial to compare the effects of preemptive antifibrinolysis of single-dose and repeat-dose TXA in RA patients undergoing TKA.

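### Null laboratory results after surgery cannot speak to the effect or safety of TXA itself in RA; Pre-D1 is the only TXA-versus-saline sample and deserves a baseline-adjusted analysis

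*Protocol article*

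**What the plan says.** The objective, in the Background section, is to "compare the effects of preemptive antifibrinolysis of single-dose and repeat-dose TXA in RA patients undergoing TKA". Under Study interventions, for Group A, "100 mL normal saline (NS) will be administrated intravenously twice daily starting from 3 days before the operation"; for Group B, "1.5 g of TXA will be given twice daily starting from 3 days before the operation". The abstract then states: "All patients will be given TXA 1.5 g 30 min before the operation". The section on venous thromboembolism prophylaxis gives everyone rivaroxaban from 12 h after surgery for 14 days.

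Fibrinolysis, inflammatory and coagulation markers "will be tested 1 and 3 days before surgery and 1, 2, 3 and 14 days after surgery". The Statistical analysis section names a t-test or Mann–Whitney test for quantitative outcomes. It singles out no visit and mentions no baseline adjustment.

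Some statements about what the trial will tell us go beyond the two regimens. The abstract says that "there is a lack of evidence with regard to the efficacy of TXA in RA patients" and that the results, in whichever direction, will feed into recommendations on using TXA in these patients. The last sentence of the Discussion says, with a hedge, that APTT, PT and TEG may help to assess the safety of TXA in RA. The Discussion's remark that "evidence is scarce in RA patients with regard to the anti-inflammatory effect of TXA" is background. The sentence after it limits the inflammation aim to comparing regimens and to the extra control that repeat dosing might give.

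**The concern.** Two statements about what this trial's results will contribute, one in the abstract and one at the end of the Discussion, refer to TXA as such. After the operation there is no TXA-free arm. If D-dimer, IL-6 or TEG look alike in the two groups at D1 to D14, a reader guided by that wording could conclude that TXA has no anti-inflammatory action, or carries no pro-coagulant risk, in RA. The data could not support either conclusion.

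The schedule does contain one randomised, blinded TXA-versus-saline comparison, at Pre-D1. It precedes surgery, the common TXA dose and rivaroxaban. It also bears on the trial's own rationale, since the Discussion justifies repeat dosing partly by a hyperfibrinolytic state already present before surgery. As described, it gets the same unadjusted test as every other visit, although an earlier sample from the same patients is collected.

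**Working it through.** **Which contrast each visit offers** (Table 1, Study interventions, Venous thromboembolism prophylaxis):

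| Visit | Group A so far | Group B so far | Contrast |
|---|---|---|---|
| Pre-D3 | start of saline | start of TXA | baseline, if sampled before the first dose (not stated) |
| Pre-D1 | saline | repeated TXA | TXA versus no TXA |
| D1, D2, D3, D14 | saline, pre-incision TXA, rivaroxaban | repeated TXA, pre-incision TXA, rivaroxaban | repeat-dose versus single-dose |

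Of the five visits after Pre-D3, one has a TXA-free arm.

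**What a postoperative null means.** Let f be the effect of TXA on a marker relative to none, P the pre-incision dose and R the repeated doses. After surgery the group difference estimates f(R+P) − f(P). This is zero if f is zero throughout, and also if f(R+P) = f(P) with both non-zero. The data cannot tell these apart. At Pre-D1 the difference estimates f(R) against no TXA, so the ambiguity does not arise. A non-zero postoperative difference is another matter: the extra doses were randomised, so it is evidence that TXA does something, though it does not measure TXA against none.

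**What Pre-D1 can detect.** The plan gives no power figure for the laboratory markers. Its sample size concerns total blood loss: 31 per arm, and 31/(1 − 0.20) = 38.75, so 39, which reproduces the stated recruitment target. How the 31 was derived is a separate matter; here 39 and 31 serve only as numbers available without and with the planned loss.

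Two-sided 0.05 and 80% power, normal approximation: detectable difference in SD units = (1.960 + 0.842) × √(2/n).

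- n = 39: 2.802 × √(2/39) = 0.63 (0.64 by the t-test calculation).
- n = 31: 2.802 × √(2/31) = 0.71 (0.72 by the t-test calculation).

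ANCOVA on the Pre-D3 value multiplies this by √(1 − r²), where r is the Pre-D3/Pre-D1 correlation. The protocol gives no r, so a range is shown:

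| r (assumed) | √(1 − r²) | n = 39 | n = 31 |
|---|---|---|---|
| 0 (unadjusted) | 1 | 0.63 | 0.71 |
| 0.5 | 0.866 | 0.55 | 0.62 |
| 0.7 | 0.714 | 0.45 | 0.51 |
| 0.8 | 0.600 | 0.38 | 0.43 |

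These figures apply to one marker at a time, on the scale analysed, with no allowance for multiple testing.

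**The case against.** The strongest reply is that the trial never sets out to compare TXA with no TXA. The objective is single versus repeat dosing, the inflammation hypothesis is about additional control, and the safety aim is stated for different regimens. All three are incremental, and D1 to D14 can address them. This stands. A reader might infer that the design is faulty or that its laboratory outcomes are uninformative; the documents do not support that.

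A reader might also infer that no postoperative comparison can reveal anything about TXA. That goes too far, because a positive difference would be evidence of a TXA effect. Only a null is ambiguous.

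Nor is Pre-D1 without a role. It is a scheduled assessment, the general two-group tests cover it, and no other marker visit is singled out either. The text does not say that Pre-D1 would be pooled with later visits or used as a baseline. A fuller analysis plan may give it a specific place, so the lack of a named key time point is not itself a fault.

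Finally, the interest in inflammation and thrombosis is largely postoperative, and Pre-D1 cannot speak to surgical trauma. That also stands and limits what Pre-D1 can be used for.

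The reply does not remove the wording in the abstract and in the last sentence of the Discussion. Both say what this trial's results may contribute, and both refer to TXA rather than to the regimens. The hedge in the second softens the claim but leaves its object unchanged.

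**Conclusion.** The concern holds in limited form. The regimen question is answerable as designed, and no figure in the plan is shown to be wrong. Two statements extend the inference to the efficacy and safety of TXA itself in RA, and a null result at D1 to D14 could not support that extension. Pre-D1 is the only scheduled TXA-versus-saline sample. The described unadjusted test would detect about 0.63 SD with 39 per arm and 0.71 to 0.72 SD with 31, so only a fairly large effect. Adjustment for Pre-D3 would lower the 39-per-arm figure to between 0.55 and 0.38 SD.

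This gain rests on an assumed correlation of 0.5 to 0.8 and on the Pre-D3 sample being taken before the first dose, which the protocol does not state. If it were taken after, it would not be a clean baseline. The number of doses received before the Pre-D1 sample is not stated either. This is a modest point of interpretation and precision.

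**What to change.** - Confirm that the Pre-D3 blood sample precedes the first study dose, and say so.
- Analyse Pre-D1 IL-6 and CRP, D-dimer and FDP, and APTT, PT and TEG by ANCOVA with the Pre-D3 value as covariate, on a transformed scale where the distribution is skewed. Identify this as the trial's only TXA-versus-no-TXA contrast.
- Reword the abstract's Discussion and the last sentence of the main Discussion so that conclusions from D1 to D14 concern repeat-dose versus single-dose TXA. State that a null there will not be read as absence of a TXA effect or of a TXA risk.
- State that Pre-D1 reflects a short preoperative exposure and does not address the response to surgery.

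The cost is a few sentences and one covariate in the model. No sample, visit or patient is added, and the primary outcomes are untouched.
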